#### Tools for youth champions and youth beneficiaries

Patient Health Questionnaire (PHQ)-9: The present study will also be using a 9-item self-report version of the Primary Care Evaluation of the Mental Disorders (PRIME-MD), a validated screening tool for identifying levels of depression among individuals (46). It is composed of 9 items to capture depressive symptoms. The total scores may range from 0 to 27 and five levels of severity varying from minimal (0–4), mild (5–9), moderate (10–14), moderately severe (15–19) and severe (20–27) (46).Perceived Stress Scale (PSS-10): A 10-item self-reporting screening tool for identifying level of personal stress and the degree to which an individual appraises their daily life circumstances as stress-inducing (47). The total score is the sum of all items, including reverse scoring for positive items (item 4, 5, 7 and 8). The total score ranges from 0 to 40 and three levels of severity ranging from low (0–13), moderate (14–26) and high (27–40) (47).Mental Health Awareness. This 19-item measure, with each item comprising three response options: false/true/do not know. ‘True’ responses to correctly worded items from this section receive a score of one, while ‘true’ responses for incorrectly worded items receive a score of zero. This is reversed for three items (items). ‘Do not know’ as a response to any item is given a score of zero. It was developed as part of a larger study on promotive intervention in college youth, in an Indian setting, via an extensive literature review, content validation by experts and 3 pilot trials covering 238 college going youth. The measure exhibited satisfactory reliability and its scores correlated positively with the measure of attitudes toward mental health and illness and showed significant changes following participation in a promotive intervention (48). Two additional items (myths/facts) pertaining to sadness vs. depression and usefulness of help seeking when distressed are planned to be included in addition (38).General Help Seeking Questionnaire (GHSQ): Help seeking inclination refers to the likelihood of seeking help from one or more sources for psychological distress (49). The tool assesses the participant’s intention to receive aid from varied sources as well as the inclination to reject /not seek help from any source (help negation). GHSQ is a flexible tool, allowing researchers to make modifications as per study requirement for instance, adapting sources of help and types of problems/issues to enhance relevance for the target population. Seven to twelve sources have been listed in previous studies and psychometric properties (internal consistency, convergent validity) have been found to be satisfactory across studies (50, 51). A 7-point Likert scale is used for ratings for each of the potential sources, varying from 1 (Extremely Unlikely) to 7 (Extremely likely) (49). In the present study, help seeking preferences from both formal and informal sources (e.g., teachers, counselors, helpline numbers, peer, guardian etc.) for emotional distress will be examined along with the item on help negation. In addition, an open-ended item for any other sources of help will be used to capture any unlisted source.Actual Help-seeking Behavior: This would be captured by enquiring about help sought within a specified time frame from one or more of the listed sources for personal/emotional problems. The list of sources would match the sources used in GHSQ. The assessment would use a checklist of items and the youth would also be given an option to briefly mention the type of issue/distress prompting the help-seeking behavior (50).Helping Giving Behaviors: Multiple choice questions would be used for the present study to assess if the youth encouraged someone who may have been experiencing mental health concerns to reach out for professional help (No, 1 person, 2 persons, more than 2 persons). Additionally, they would be asked if the encouragement provided actually led to the person seeking help (yes/No/not sure) (52).

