Effectiveness	Mean score of: Depressive symptoms-PHQ-9 Perceived stress-PSS10 Help seeking inclination-GHSQ Help-Seeking Behavior	Proportion of youth champions who were approached by distressed students for help Proportion of distressed students referred by youth champions to gatekeepers or school leaders Proportion of students who accessed self - help modules	Proportion of gatekeepers who were approached by distressed students for help Proportion of distressed students referred by gatekeepers	Administrative data and records self-reported/log books maintained by gatekeepers and youth champions
Sustainability: Extent to which the intervention is maintained/institutionalized	Key informant interviews by district authorities and leaders			Testimonials by gatekeepers and youth champions and youth beneficiaries if possible

**Described in detail under statistical analysis heading.

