### Study outcomes

#### Primary outcomes

The present study focuses on the following primary outcomes:

Reduction in suicide risk factors: This is measured by a decrease in perceived stress levels and depressive symptoms among students in educational institutions using validated scales.Improvement in help-seeking behavior: This is measured by a rise in the proportion of individuals engaging with services/aid for mental health.

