### Data collection

Data collection will be conducted in a retrospective manner to document the activities undertaken and their frequency across three phases: the pre-implementation phase (e.g., initial meetings, development of training manuals), the refinement phase (pilot testing and adaptation of the intervention), and the implementation and sustenance phase (trainings, meetings, and other activities carried out as per the refined model framework). The activities will be cost separately for each type of educational institution, considering the heterogeneity in functioning and resource use.

For each category of activity, the corresponding quantity of resources for which financial allocations were made will be assessed through stakeholder interviews with implementation teams and a review of relevant records. Resource prices will be obtained from records on actual financial allocations made, supplemented by information from personnel interviews, administrative documents or standard cost databases. For activities performed by the research team to support the implementation of the strategies, shadow pricing will be applied to document the full implementation costs to facilitate potential scale-up. In contrast, activities conducted exclusively for research and evaluation purposes will be excluded from the costing analysis. Likewise, the opportunity cost of undertaking implementation activities will not be considered.

In parallel, the evaluation will capture the impact of the suicide risk reduction strategy on healthcare-seeking behaviors, specifically by measuring the change in the number of students accessing health services following referral by educational institution staff at three time points: baseline (pre-intervention), midline (6 months), and endline (12 months). The incremental costs of outpatient consultations resulting from these referrals will also be incorporated into the final cost of the implementation package.

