### Quantitative analysis

Data analysis would be done with IBM SPSS software (version 25.0) and R software (version 4.5.1). Nominal or categorical variables would be summarized as frequency and percentages. Continuous variables will be summarized as mean and standard deviation when normally distributed and as median and interquartile range (IQR) when non-normally distributed. Frequency and percentages will be used to describe categories of coverage (full/partial/not attempted), adoption, and reach of intervention within a cluster. The coverage will be compared across different categories (school types, study sites, urban/rural) using Chi-square test or fisher exact test.

Both clinical and implementation outcomes will be recorded as binary variables. Scores above or equal median will be considered as yes and below median as no for clinical outcomes while for implementation outcomes all the institutes will be evaluated as high performing (implemented 2 or more interventions) or low performing (implemented less than 2 interventions) based on the level of implementation. The study will employ the mixed effects logistic regression model within the generalized linear mixed models (GLMMs) framework to predict both types of binary outcomes, allowing for inclusion of both random and fixed effects. Covariates for assessing coverage of institutes will include type of institute; rural/urban location; gatekeeper to student ratio; youth champions to youth beneficiary ratio in modeling equation. For predicting help seeking behavior of students, covariates will include age and gender of student, education and occupation of parents, any known stressor in family such as recent death of close one; single parent; any past history of mental illness or suicide in family; etc.Time series analysis will be used for mathematical projection of the help seeking behavior of the youth beneficiaries in the study clusters. Forecasting model ARIMA (Autoregressive Integrated Moving Average) will be used to make projections till 12–18 months after the study period based on the data obtained at 3 time points (0, 6, 12 months).

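### The primary help-seeking outcome is not fixed consistently: the plan does not settle which help sources count or whether it is a proportion, a mean score or a median split

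*Protocol article*

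**What the plan says.** All of the text is in the protocol article.

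- **Primary outcomes:** improvement in help-seeking is measured by "a rise in the proportion of individuals engaging with services/aid for mental health".
- **Tools for youth champions and youth beneficiaries, Actual Help-seeking Behavior:** the checklist asks about "help sought within a specified time frame from one or more of the listed sources for personal/emotional problems". On its content: "The list of sources would match the sources used in GHSQ".
- **Same section, General Help Seeking Questionnaire (GHSQ):** in this study its list covers "both formal and informal sources (e.g., teachers, counselors, helpline numbers, peer, guardian etc".
- **Table 4, Effectiveness row (under Implementation strategies):** the entries below the mean-score label include "Help seeking inclination-GHSQ Help-Seeking Behavior".
- **Quantitative analysis:** "Scores above or equal median will be considered as yes and below median as no for clinical outcomes". The same section plans mixed effects logistic regression and lists covariates for predicting students' help-seeking.
- **Data collection (cost analysis):** a separate measure is the "change in the number of students accessing health services following referral by educational institution staff", at baseline, 6 and 12 months.

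The package is also relevant. Table 1 and the youth engagement section provide for at least two youth champions per class, trained to hold supportive conversations with distressed peers and to encourage them to seek further help.

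**The concern.** A primary outcome needs one rule that turns a student's answers into an event. Here the outcome definition speaks of services or aid, the tool pools formal and informal sources, the results table asks for a mean score, and the analysis section splits at the median. These can give different answers from the same data.

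Which sources count matters more than usual in this study because delivering the package creates informal contact. If any ticked source is an event, a conversation with a youth champion counts the same as a visit to a counselor. A reader told that engagement with mental health services or aid has risen could not tell from that number whether more students had reached a service. If the choice stays open, it could also be made after the results are known.

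**Working it through.** **Step 1. The four descriptions side by side.**

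| Place | Form of the outcome | Sources that count |
|---|---|---|
| Primary outcomes | Proportion | Services/aid, not listed |
| Actual Help-seeking Behavior | Checklist by source, no scoring rule | Formal and informal, same list as the GHSQ |
| Table 4, Effectiveness | Mean score | Not stated |
| Quantitative analysis | Yes if at or above the median | Not stated |

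No passage links the checklist to the proportion. A student who spoke only to a friend is an event if any listed source counts, and a non-event if only services count.

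**Step 2. The median rule applied to a checklist.** Suppose the score is the number of sources ticked (an assumption, since no scoring is given). If more than half of the students tick none, the median is 0 and every student is a yes. If the median is 1, yes means any source. If it is 2, yes means at least two sources. The event would depend on the data, and in none of these cases does it mean use of a service.

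**Step 3. How far informal help can move an any-source proportion.** The article gives no help-seeking rates, so there is no figure to reproduce and every rate here is assumed. Let i be the proportion using informal help, f the proportion using a service, and v the share of service users who also use informal help. Then any-source = i + f(1 − v).

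- Service use doubles, 5% to 10%, with i = 60% and v = 75%: 0.60 + 0.05 × 0.25 = 0.6125 becomes 0.60 + 0.10 × 0.25 = 0.625. The gain is 1.25 points against 5 points in service use.
- Informal help rises from 60% to 70%, service use flat at 5%: 0.6125 becomes 0.70 + 0.0125 = 0.7125. The gain is 10 points with no added service use.
- Service use halves, 10% to 5%, informal help rises from 60% to 70%, the two independent: 1 − 0.4 × 0.90 = 0.64 becomes 1 − 0.3 × 0.95 = 0.715. The any-source proportion gains 7.5 points while service use falls.

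If the two kinds of help are independent and informal help stays at 20%, 40%, 60% or 80%, doubling service use from 5% to 10% raises any-source by 5 × (1 − i) points, that is 4, 3, 2 or 1.

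**Step 4. Illustrative power.** Take n = 400 × 0.9 = 360 paired responders, a within-student correlation of 0.5 (the article's assumption for PHQ-9 scores, borrowed here) and independent students. With p11 = p0·p1 + 0.5√(p0(1−p0)p1(1−p1)), b = p0 − p11 and c = p1 − p11, the main term of McNemar power is Φ[(√n·|c − b| − 1.96√(b + c)) / √(b + c − (c − b)²)]. The small opposite tail is added.

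| Change | Power |
|---|---|
| Services only, 5% to 10% | 0.94 |
| Any-source, 61.25% to 62.5% | 0.08 (0.05 at v = 90%, 0.12 at v = 60%) |
| Any-source, 61.25% to 71.25% | 0.98 |

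These values move a good deal with the assumptions:

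- A design effect of 2 gives 0.69, 0.06 and 0.80.
- If 400 is meant per site, n = 8 × 360 = 2,880 and the second row becomes 0.28 (0.60 at v = 60%).
- Treating the time points as independent samples gives 0.72 in place of 0.94.

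**The case against.** The strongest reply rests on the word aid. The article's own description of the GHSQ uses that word for help from varied sources, so services/aid can be read to cover the mixed list. A reader might infer a flat contradiction between the outcome definition and the checklist. The documents do not support that. They show a definition left unresolved, and the checklist text never says that any tick is a primary event.

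A reader might also infer that the study could not tell whether service use changed. That is too strong. The checklist records each source, so a formal-source proportion can be derived, and the costing work counts access after staff referral. That count does not replace the outcome, however: it serves the costing and covers referred students only.

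A third inference would be that only formal sources may be primary. Peer support is a designed component, so more help from peers may be an intended effect. Which event is primary is partly the investigators' choice of estimand.

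It can further be said that deriving a binary variable is work for an analysis plan not shown here, and that the mean of a yes/no variable is itself a proportion. Both are fair in general. But the article prints a median rule and a mean score beside a proportion, and that printed text needs reconciling whatever an analysis plan adds.

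**Conclusion.** The point stands as an inconsistency in how a primary outcome is defined. Four sections leave open which sources count and which summary measure applies, and the median rule does not yield the stated proportion. Given the peer-support component, an any-source version could rise without added service use or hide a change in it.

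The direction of that risk follows from the text and simple arithmetic. Its size does not. The 5%, 60% and 75% are assumptions, the correlation is borrowed from PHQ-9, clustering is ignored in the main figures, and the planned model is mixed logistic regression and not McNemar. The power values are illustrations, not estimates for this study. No data are lost, so this is a correction that should be made and not a fatal fault.

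**What to change.** Reconcile Primary outcomes, the Actual Help-seeking Behavior entry, Table 4 and Quantitative analysis as follows:

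1. Define the outcome once, as a yes/no proportion taken from the checklist.
2. State before analysis which checklist sources count as services/aid, including whether teachers or gatekeepers and youth champions do.
3. Always report the formal-source and informal-source proportions separately, so that any claim of increased service engagement rests on the formal-source proportion.
4. Remove the mean-score label and the median split for this outcome.

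The cost is wording and a derived variable. The checklist already records sources, so no new data are needed. The formal-source proportion will be lower than an any-source one and may look less favourable.

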#### Secondary outcomes

The expected secondary outcomes are as follows:

Proportion of educational institutes who started integrating the model and forming a school wellness team.Incremental cost of the implementation of the model.

### Implementation outcomes

Implementation outcomes serve as indicators of success of implementation and are also seen as proximal indicators of implementation processes.

#### Implementation outcomes

Implementation outcomes serve as indicators of success of implementation and are also seen as proximal indicators of implementation processes (57). The implementation outcomes are aligned with the RE- AIM framework (17). These would capture ‘Adoption’ at setting level, ‘Reach’ and ‘Effectiveness’ at individual level, ‘Implementation’ through documenting feasibility, fidelity, appropriateness, acceptability and observations on ‘Maintenance’ of the program activities in the last phase of the project when the support from research-team is gradually withdrawn.

The implementation process will be evaluated by the COM-B model (58) of the Behavior Change Wheel (BCW). As per this model, there are 3 key factors & multiple sub-factors capable of changing behavior, namely capability, opportunity, and motivation.

Program learning shall be documented using the qualitative methods (FGD, IDI), including listing barriers and facilitators, reasons for not following through with treatment, follow-up consultations (provider plus beneficiary), feasibility and acceptability of the training module/program through questionnaires and FGDs, technical and logistical challenges in delivering the program, challenges faced by staff during the completion of the course and their subsequent engagement (reaching out and referring), difficulties encountered when participating in the online refresher training, and the overall satisfaction level of staff post-training. The timeline for all the study-related activities is provided in the Gantt chart (Table 5).

**TABLE 5 tab5:** Study timeline and Gantt chart.

Activities	Year 1												Year 2												Year 3											
Approvals - Ethical, ICMR, Govt officials																																				
Recruitment of staff, training, identifications of schools/colleges																																				
Preparatory phase (resource mapping, formative research, content development, translation)																																				
Phase 1 - Implementation and iteration cycle of model M0 + to reach refined Model (Mref)																																				
Phase 2 - Implementation of Mref model																																				
Annual progress report																																				
Final report and dissemination of results																																				

### Cost analysis of the mental health and well-being improvement intervention model

#### Conceptual framework

The implementation costs will be estimated using the pragmatic approach (59), that integrates time-driven activity-based costing (TDABC) informed by process mapping (60) and guided by an implementation science framework (54) for specifying and reporting strategies for implementation.

In the first step, process mapping will be conducted to capture detailed information on actors (who perform the activities), actions (what is done), temporality (when the activity occurs), and dosage (frequency and duration of activities) in line with the Proctor et al. framework. Subsequently, the costs of the implementation strategies will be estimated by identifying the quantity of resources required to execute the activities, and assigning appropriate prices to these resources.

The assessment of costs will be undertaken from a payer’s perspective, which reflects the direct financial expenditures incurred by the government for the implementation of the strategies. This perspective captures the additional resources required for implementing the intervention, including expenditure on personnel, equipment, etc., while excluding costs borne by patients, caregivers, or society at large. By adopting this perspective, the analysis will generate policy-relevant estimates of the financial commitments necessary for scaling and sustaining the implementation package within the existing system.

### Data collection

Data collection will be conducted in a retrospective manner to document the activities undertaken and their frequency across three phases: the pre-implementation phase (e.g., initial meetings, development of training manuals), the refinement phase (pilot testing and adaptation of the intervention), and the implementation and sustenance phase (trainings, meetings, and other activities carried out as per the refined model framework). The activities will be cost separately for each type of educational institution, considering the heterogeneity in functioning and resource use.

For each category of activity, the corresponding quantity of resources for which financial allocations were made will be assessed through stakeholder interviews with implementation teams and a review of relevant records. Resource prices will be obtained from records on actual financial allocations made, supplemented by information from personnel interviews, administrative documents or standard cost databases. For activities performed by the research team to support the implementation of the strategies, shadow pricing will be applied to document the full implementation costs to facilitate potential scale-up. In contrast, activities conducted exclusively for research and evaluation purposes will be excluded from the costing analysis. Likewise, the opportunity cost of undertaking implementation activities will not be considered.

In parallel, the evaluation will capture the impact of the suicide risk reduction strategy on healthcare-seeking behaviors, specifically by measuring the change in the number of students accessing health services following referral by educational institution staff at three time points: baseline (pre-intervention), midline (6 months), and endline (12 months). The incremental costs of outpatient consultations resulting from these referrals will also be incorporated into the final cost of the implementation package.

